## Abstract

**Background:**

The hallmark symptom of heart failure (HF) is severe exercise intolerance. Fortunately, accumulated evidence suggests that exercise programs improve physical performance, enhance autonomy in daily activities and quality of life, and reduce cardiovascular and other hospitalizations. Recently, experimental studies have explored the application of non-invasive brain stimulation techniques, especially transcranial direct current stimulation (tDCS), aiming to improve physical performance due to its ability to modulate brain functioning. The primary objective of the present study is to evaluate the effects of anodal tDCS associated with aerobic exercise on the functional capacity of patients with HF with reduced ejection fraction (HFrEF). Secondary objectives are to compare the effects of tDCS associated with aerobic exercise *vs*. sham-tDCS associated with aerobic exercise on cardiopulmonary exercise capacity; inflammatory cytokines; and quality of life.

**Methods:**

This is a two-arm, prospectively registered, randomized trial with concealed allocation, double-blind, and intention-to-treat analysis. Forty-four patients with HFrEF will be recruited. The experimental group will undertake 25–30 min aerobic exercise training associated with tDCS, for 4 weeks. The control group will undergo the same aerobic exercise training, but with sham-tDCS. The primary outcome will be functional performance by the 6-min walk test. Secondary outcomes will include cardiopulmonary exercise capacity, inflammatory cytokines, and quality of life. Outcomes will be collected by a researcher blinded to group allocation at baseline (T0) and after 4 weeks of intervention (T1).

**Discussion:**

Although previous studies have investigated the combined effect of tDCS on T3 area and physical performance and have suggested that tDCS could have reduced ratings of perceived exertion by affecting the activity of the insular cortex, and therefore increase exercise tolerance, this study is the first to evaluate the effects of the addition of anodal tDCS to aerobic exercise training for improving physical and functional performance, decreasing the perceived exertion, altering the quantification of inflammatory cytokines, and improving the subclinical values of the cardiopulmonary test in patients with HFrEF, which could result in an important advance in cardiac rehabilitation for patients with chronic HF.

**Trial registration:**

Brazilian Registry of Clinical Trials (ReBEC) RBR-10w787j6. Registered on 25 April 2023. https://ensaiosclinicos.gov.br/pesquisador

## Background

Currently, cardiovascular diseases constitute the main group of diseases in causes of death worldwide and are responsible for premature deaths, loss of quality of life, and biological and social impacts [13, 15, 28]. Heart failure (HF) is a common terminal symptom of many cardiovascular diseases [11], and as part of this group, it is related to high direct hospitalization costs and indirect costs, with a high burden of morbidity for patients [27, 33].

The hallmark symptom of HF is severe exercise intolerance, which is multifactorial and attributed to central and peripheral pathophysiological mechanisms, such as impaired cardiorespiratory reserve, excessive systemic vascular resistance, impaired vasodilation capacity, abnormal redistribution of blood flow and muscle perfusion, and decreased mitochondrial volume density and skeletal muscle function [32]. Heart injury causes an increase in the neurohumoral activity of some systems, such as the sympathetic nervous system, which triggers inflammation and oxidative stress, culminating in several alterations in the musculoskeletal system, including a reduction in strength [17]. Elevated levels of interleukin-6 (IL-6) and tumor necrosis factor (TNF-alpha) were described as important factors for the progression of chronic HF [10, 17]. Exercise intolerance, chronic fatigue, and inability to perform activities are the main symptoms of HF and are associated with poor quality of life and adverse outcomes [3, 8, 14, 33].

Fortunately, accumulated evidence suggests that exercise programs improve physical performance, lessen left ventricular remodeling, improve autonomy in daily activities and quality of life, and reduce cardiovascular and other hospitalizations [4, 11, 13, 16, 23, 25, 32]. Based on principles of exercise physiology, performance depends on the integrative response of the pulmonary, circulatory, and musculoskeletal systems. Goes-Santos et al. [11] suggest that there is a link between an increase in physical capacity and amelioration in neurovascular control and skeletal myopathy in exercise-trained patients with HF with reduced ejection fraction (HFrEF). Peripheral adaptations, particularly in skeletal muscle, are the primary mechanism for increasing maximal oxygen uptake (*V̇*O_2_max) after exercise training in patients with HF, and the reason may be that, compared with cardiac muscle, skeletal muscle is more plastic and has the potential for rapid, large improvements in function after even a brief period of exercise [28].

Recently, experimental studies have explored the application of noninvasive brain stimulation techniques, especially transcranial direct current stimulation (tDCS), aiming to improve physical performance due to its ability to modulate brain functioning [2, 18, 21]. Even more interestingly, tDCS may have a moderate positive impact on performance levels [30], and both tDCS and aerobic exercise are capable of modulating cognitive functions, hemodynamic activity, brain activity, and perceived exertion in submaximal exercise [19, 31]. A possible target for tDCS is applying over the left temporal cortex to modulate the insular cortex (IC), which is implicated in the control of cardiac autonomic function, resulting in increased parasympathetic modulation at rest and during exercise, and delaying the rate variability threshold would increase the time exercising with a lower cardiovascular load, which could postpone fatigue [12, 19]. Okano et al. [24] and Montenegro et al. [20] studied the effects of anodal tDCS in IC and observed a decrease in dyspnea and fatigue and faster recovery after exercise in athletes in their trials.

Based on these studies, we hypothesized that patients with HFrEF who received anodal tDCS in IC associated with aerobic exercise, when compared to those submitted to sham-tDCS associated with aerobic exercise, will have better physical and functional performance, decreasing perceived exertion, altering the quantification of inflammatory cytokines, and improving the subclinical values of the cardiopulmonary test (*V̇*E/*V̇*CO2 slope and OUES), thus innovating in terms of therapeutic possibilities for so many patients with the same pathological condition in Brazil and worldwide (Fig. 1). The primary objective of the present study is to evaluate the effects of anodal tDCS associated with aerobic exercise on the functional capacity of patients with HFrEF. Secondary objectives are to compare the effects of tDCS associated with aerobic exercise *vs*. sham-tDCS associated with aerobic exercise on (1) cardiopulmonary exercise capacity, (2) inflammatory cytokines, and (3) quality of life.

**Fig. 1 Fig1:**
[figure not shown]
Illustration of the benefits of the intervention

## Methods

### Study design

The ELETRIC study is designed to investigate the effects of noninvasive brain stimulation in patients with HF (*Eletroestimulação em Insuficiência Cardíaca*, in Portuguese).

A clinical, randomized parallel-design 1:1 ratio allocation, controlled, blinded assessors, participants and therapists, and intention-to-treat analysis will be carried out by the Federal University of Amazonas (Universidade Federal do Amazonas) at the University Hospital Getúlio Vargas, in the city of Manaus, North Brazil (Fig. 2). The study was approved by the ethics committee (CAAE 64652122.0.0000.5020) and registered by ReBEC (Brazilian Registry of Clinical Trials), registry RBR-10w787j6. The study protocol adheres to the SPIRIT 2013 recommendations.

**Fig. 2 Fig2:**
[figure not shown]
Proposed trial design

### Eligibility criteria

The volunteers will be included in the study if they meet the following:Adult men or womenAge equal to or older than 18 years oldClinically stable HF (ischemic or nonischemic) for at least 3 months before randomizationLeft ventricular ejection fraction of less than 40% evaluated by echocardiogramFunctional class II or III by New York Heart AssociationOptimized pharmacological treatment

The volunteers will be excluded if they present the following:Stable and unstable anginaSevere cardiac arrhythmiasAdvanced atrioventricular block (second and third degree)Symptomatic coronary artery diseasePacemaker or implantable ventricular defibrillatorsDecompensated HF less than 3 monthsMetabolic syndromes linked to the thyroid or liverBody mass index (BMI) less than 18.5 and greater than 34Acute myocardial infarction and/or cardiac surgery for less than 6 monthsUncontrolled diabetes, high blood pressure, and dyslipidemiaDiagnosed lung disease, such as exercise-induced asthma and pulmonary fibrosisOrthopedic or musculoskeletal disorders that limit physical exercise (such as osteoarthritis in the lower limb and/or spine)Neurological and/or cranial alterations that prevent the application of tDCSDiagnosed seizuresRegular practice of physical exercise in the last 12 monthsPregnantSmokersAlcoholicsImpaired cognitive status that compromises the understanding of the steps and completion of the study protocol, screened by the Mini-Mental State Examination (MMSE). The cutoff scores are 26 for people with high levels of education, 18 for people with elementary and middle levels, and 13 for illiterate people.

### Initial assessment

One of the researchers ([name]), in a reserved room at the University Hospital Getúlio Vargas, will explain the study and deliver the informed consent form with time for the patient to think and respond about his/her participation.

Additionally, the consent form will inquire whether participants consent to the utilization of their data in the event of their withdrawal from the trial. Participants will also be requested to grant permission for the research team to share pertinent data with individuals affiliated with the participating universities or regulatory authorities, as applicable. It is important to note that this trial does not involve the collection or storage of biological specimens.

Volunteers will undergo an initial assessment, which will collect information regarding the current illness, past illness, comorbidities, drugs in use along with dosage, systolic (SBP, mmHg) and diastolic (DBP, mmHg) blood pressure, heart rate (HR, bpm), respiratory rate (RH, rpm), body composition (weight, height, and BMI), peripheral oxygen saturation, and perception of exertion by Borg CR-10.

Cardiac function will be assessed by two-dimensional transthoracic echocardiography supplemented with M-mode, pulsed, tissue, and color Doppler, according to the recommendations of the American Society of Echocardiography (American Society of Echocardiography, 2005). Measurements of the cardiac cavities and evaluation of ventricular systolic and diastolic functions will be performed. The cavities measured will be left ventricular diastolic diameter (LVDD), right ventricular diastolic diameter (RVDD), and left atrial volume indexed by body surface (LAEi). Ventricular systolic function will be assessed by capturing left ventricular ejection by Simpson’s method (LVEF), by the systolic velocity of the lateral mitral annulus (lateral S′), and by the systolic velocity of the tricuspid annulus (tricuspid S′). The left ventricular diastolic function will be evaluated by the relationship between the E wave of the mitral flow and the E wave of the mitral annulus on tissue Doppler (E/E′ ratio) and by the diastolic velocity of the lateral mitral annulus (lateral E′).

All participants will be submitted to the Mini Mental State Examination (MMSE), an instrument developed by Folstein, Folstein, McHugh (1975), consisting of two parts, one covering orientation, memory, and attention (whose maximum score is 21 points) and the other about specific skills, such as naming and understanding (whose maximum score is 9 points), totaling a score of 30 points; higher values indicate greater cognitive performance. The score can be influenced by the individual’s education, following the proposal by Brucki et al. [5]: 20 points for illiterates, 25 points for people with 1 to 4 years of schooling, 26.5 for 5 to 8 years, 28 for those aged 9 to 11 years, and 29 for those aged over 11 years. Those with lower scores in their education category will be excluded from the study.

### Primary outcome measurements

The primary outcome is functional performance.

#### Six-minute walk test (6MWT)

The 6MWT will be used to assess the functional capacity of the participants [7]. The 6MWT will be held in a flat corridor 30 m long. The subjects will be oriented and encouraged to walk as far as possible in a stretch marked with colored tapes on the ground, for a period of 6 min with standardized phrases. It will be emphasized that if there is a need to interrupt the route, you must do so. The test will be performed twice, with an interval of 30 min between them, according to the recommendations of the ATS (ATS Committee on Proficiency Standards for Clinical Pulmonary Function Laboratories, [1]). After that, the test with the best performance (distance covered in meters) will be selected for analysis. In each test, the subject will remain for 5 min at rest sitting, then the same time at rest in the orthostatic position, and in sequence, will start the exercise. Performance recording will be performed at the peak of the exercise, as well as the presence and duration of pauses during walking and desaturation >4%, if any. A recovery time of 6 min after the exercise will be considered. HR (Polar H10, Polar, Kemple, Finland), BP (BIC sphygmomanometer, Itupeva, São Paulo) by the auscultatory method (Littman Classic II stethoscope, USA), SpO_2_ by digital oximeter (Nonin, model 2500, Minneapolis, MN), and the modified scale of perceived exertion Borg CR-10 will be used and their values recorded in the moments of rest sitting pretest, exercise peak, and first, third, and sixth minutes of recovery.

### Secondary outcome measurements

Secondary outcomes are cardiopulmonary exercise capacity (CPX), inflammatory cytokines, and quality of life.

#### Cardiopulmonary exercise test

Physical capacity will be assessed by CPX on a CG-04 ergometric bicycle (Inbramed, Porto Alegre, Brazil) with data directed to the breath-to-breath ergospirometer (PNOE, ENDO Medical, CA, USA) with a ramp protocol of 5–10 watts per minute. The volunteer must use a mask and mouthpiece system in which there is a bidirectional digital volume transducer, that is very light and precise, and capable of measuring lung volumes. The subjects will be familiarized with the exercise bike and with the Borg CR10 scale. Volunteers will be encouraged to perform the test until exhaustion. The test will be carried out together with a cardiologist medical professional, so that it is possible to detect any cardiac arrhythmias as well as assistance in the event of any intercurrences and a trained physiotherapist. The protocol will consist of the following phases: (I) rest period of 5 min sitting on the bicycle, (II) warm-up with free load for 3 min, (III) incremental phase in the ramp protocol with a cadence of 60 rotations per minute, (IV) 1-min active recovery with free load, and (V) passive recovery of 5 min standing on the bicycle. A 12-lead electrocardiogram (ECG) will be continuously monitored during the test, and blood pressure will also be recorded before the test, every 3 min during exercise and in the recovery period. The Borg CR-10 dyspnea scale will also be used to assess muscle fatigue in the lower limbs and shortness of breath during the test. The test will be interrupted if the patient presents physical exhaustion and/or presents one or more of the following criteria: (I) maximum/leg fatigue or dyspnea; (II) angina or electrocardiographic evidence of ischemia or malignant arrhythmia (ventricular tachyarrhythmia, bigeminy, and [atrioventricular and branch] blocks); (III) pressure changes with an increase greater than 220 mmHg in systole and above 100 mmHg in diastole; (IV) SpO_2_ drops to values ≤ 88%; and (V) patient request interruption of the test. Subjects will be encouraged to reach the maximum capacity limited by symptoms, characterized by a *V̇*CO_2_/*V̇*O_2_ ratio (RER) ≥ 1.1. The metabolic variables will be measured by the PNOE ergospirometer (ENDO Medical, CA, USA), and the gas analysis for the primary outcome will measure the absolute peak *V̇*O_2_ (mL/min), the corrected peak *V̇*O_2_ (mL/kg/min) and production of carbon dioxide (*V̇*CO_2_, mL/min). The variables slope of minute ventilation by CO_2_ exhalation (*V̇*E/*V̇*CO_2_ slope) and O_2_ consumption efficiency (OUES) will be evaluated during the cardiopulmonary test and before and after aerobic training. For variable calculations, the *V̇*E/*V̇*CO_2_ slope will be obtained by linear regression analysis of the relationship between *V̇*E and *V̇*CO_2_. Additionally, the relationship between *V̇*O_2_ and *V̇*E, expressed by the efficiency of oxygen consumption (OUES), will be determined by the logarithmic curve using the following equation: *V̇*O_2_ =a*log *V̇*E + b, where the constant “a” represents the rate of increase of V̇O2 in response to *V̇*E increment (Myers et al., [22]).

#### Inflammatory profile analysis

The inflammatory profile evaluation, including IL-1β, IL-6, IL-12p70, and TNF, which have a pro-inflammatory profile, and IL-10, which has an anti-inflammatory profile, was quantified using cytometric bead arrays (BD™ Human Inflammatory Cytokine kit (BD Biosciences, San Diego, CA, USA), according to the manufacturer’s instructions. Samples were acquired in a FACSCanto II (BD Biosciences, San Jose, CA, USA), and FCAP-Array software v3 (BD Biosciences, San Jose, CA, USA) was used for data analysis. Data were reported in picograms per milliliter (pg/mL) concentrations, according to the standard curves provided in the kits.

The pre- and post-assessment will be performed at the same hour, in a room with a controlled temperature (18 to 22 °C).

#### Quality of Life Questionnaire

The Minnesota Living with Heart Failure Questionnaire (MLHFQ) is an important tool to assess the limitations that are often associated with how much heart failure prevents patients from living as they would like. It is presented as the most-used instrument internationally and has great reliability, it was developed specifically for heart failure and consists of 21 questions [9]. The response scale for each question ranges from 0 (no) to 5 (too much), where 0 represents no limitations and 5 represents maximum limitations. These questions involve a physical dimension (from 1 to 7, 12, and 13) that is highly interrelated with dyspnea and fatigue, an emotional dimension (from 17 to 21) and a general dimension, related to financial considerations, medication side effects, and lifestyle (numbered 8, 9, 10, 11, 14, 15 and 16) which, added to the previous dimensions, form the total score. The last month should be considered to answer the questions.

### Intervention

Clinical assessments will be performed at baseline (T0) and at the end of 4 weeks (T1), consisting of a symptom-limited cardiopulmonary test, 6MWT, quality of life assessment, and laboratory tests (Table 1).

**Table 1 Tab1:**
[figure not shown]
Schedule of enrollment, interventions, and assessments

*−T*_*1*_, baseline assessment before randomization; *T*_*0*_, allocation; *T*_*1*_, period of interventions; *T*_*x*_, analysis of interventions

The experimental group will be submitted to anodal tDCS over the left temporal region corresponding to the T3 area according to the International 10/20 Electroencephalogram system, and the cathode will be positioned over the right supraorbital area to modulate the insular cortex during continuous aerobic exercise with a constant current intensity of 2 mA for 20 min in each session. The control group will undergo sham tDCS during continuous aerobic exercise, with electrodes positioned in identical regions to the experimental group. To ensure blinding, an envelope will be made available with a numerical sequence to be used in the device for applying tDCS, whose study mode allows active stimulation during the 20 min of intervention (experimental group) or active stimulation only for a few seconds and cessation of stimulation (control group). Thus, participants, evaluators, and applicators of the research protocols will be blinded. Although no current is applied, sham stimulation mimics sensations from active tDCS, corroborating the blinding of the study. They all will perform three times/week, for a total of 12 sessions in 4 weeks.

Each aerobic exercise session will consist of three phases: warm-up, continuous aerobic exercise, and cool-down. The warm-up will be performed on an ergometric bicycle for 5 min with free load. Continuous aerobic exercise will be performed on an ergometric bicycle, as follows: during the first week, exercises will be performed for 15 min, workload will be selected by Borg 3–4 and/or an anaerobic threshold; for the next 3 weeks, the workload will be selected by Borg 3–4 and/or 60–70% peak HR in cardiopulmonary exercise test (HR will be used for training safety), for 25–30 minutes, maintaining rotation of 60 rpm every week. Cooling down will also be performed on the ergometric bicycle for 10 min with a free load (Table 2).

**Table 2 Tab2:** Frequency, intensity, time, and type (FITT) of aerobic training

Phase	Frequency	Intensity	Time	Type
Warm-up	3 days/week	Free load	5 min	Ergometer bicycle
		Week 1: Borg 3–4 and/or anaerobic threshold	15 min	Ergometer bicycle
Continuous aerobic exercise	3 days/week			
		Weeks 2–4: Borg 3–4 and/or 60–70% peak HR in CPX	25–30 min	Ergometer bicycle
Cool-down	3 days/week	Free load	10 min	Ergometer bicycle

*HR* Heart rate, *CPX* Cardiopulmonary exercise test

In all sessions, the following will be monitored: heart rate by heart rate monitor (Polar H10, Polar, Kempele, Finland), partial oxygen saturation (SpO_2_) by pulse oximeter, and perceived exertion, measured by the Borg scale CR-10 every minute, which will be a criterion for increasing the load in training, as well as for interruption.

There are no restrictions regarding concurrent care during the trial. Furthermore, it is emphasized that patients will receive concurrent clinical treatment alongside physical training, and any changes in dosage or medication alteration will be recorded.

### Criteria for discontinuation

The criteria for discontinuation are worsening of symptoms, clinical instability, and emergence of serious infectious or viral diseases that are difficult to control.

### Sample size

For the sample size estimation, the following main outcome was *the* distance covered in the 6MWT. As there are no studies that have previously evaluated these outcomes, we used Du et al. [7] as the parameter of the minimal clinically important difference (MCID) value of 6 WMT in HF patients. The increase of 30 m was described as the mean value among studies. To calculate the effect size in the present study, we accepted 30 m of physical capacity improvement as the MCID to the control group (sham-tDCS during aerobic exercise) and, empirically, we chose 45 m of physical capacity improvement as the MCID to the experimental group (anodal tDCS during aerobic exercise). The effect size calculation was 0.41 Cohen’s *F* value. Therefore, we used the following parameters as sample size calculations for the ANOVA two-way test between factors: effect size of 0.41 by Cohen’s *F*, *α* = 5%, *β* = 80%, 2 groups and 2 measurements, and correction between measurements of 0.5. A total of 38 volunteers were reached,however, with the possibility of sample loss of 20%, a sample of 44 participants was estimated, 22 for the experimental group and 22 for the control group. For the calculation, the statistical program G*Power 3.1 (University of Dusseldorf, Dusseldorf, Germany) was used.

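### Cohen's f = 0.41 for gains of 30 m and 45 m rests on an unstated SD of 18.3 m; at that SD, 38 completers give 69% power for a 15 m difference in change, not 80%

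*Protocol article*

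**What the plan says.** The Sample size section sizes the trial on the "distance covered in the 6MWT". The planning source is used for a minimal clinically important difference: "The increase of 30 m was described as the mean value among studies". The two arms are then given gains: "we accepted 30 m of physical capacity improvement as the MCID to the control group" and "empirically, we chose 45 m of physical capacity improvement as the MCID to the experimental group". From these the section states "The effect size calculation was 0.41", as Cohen's f. The remaining inputs are described as "sample size calculations for the ANOVA two-way test between factors", with alpha 5%, 80% (printed as beta, evidently meaning power), and "2 groups and 2 measurements, and correction between measurements of 0.5". The result is 38 participants, raised to 44 for losses.

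No SD, variance or confidence interval for walk distance or its change appears in that section or elsewhere in the article. The Statistical analysis section plans a two-way ANOVA and says that covariates may be added. The examples it lists do not include baseline walk distance.

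**The concern.** Cohen's f is the spread of the group means divided by the within-group SD. The section presents f as calculated, yet gives only the means, so the quantity that determines the sample size cannot be checked. The gains are changes from baseline, while the test used for sizing compares group means averaged over both visits. The implied SD, and the power it buys, therefore depend on which contrast is meant.

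At stake is the reading of the primary result. If 38 completers give materially less than 80% power for 15 m, a non-significant result could be taken as evidence against the stimulation from a trial described as adequately powered.

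**Working it through.** **Inputs (Sample size section).** Difference 45 − 30 = 15 m; f = 0.41; alpha 5%; two groups; m = 2 measurements; correlation ρ = 0.5; N = 38. Allocation is 1:1 (Study design), so 19 per arm.

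**1. Reproducing the plan's figure.** For the repeated-measures between-factors test, λ = f²·N·m / (1 + (m − 1)ρ) with 1 and N − 2 degrees of freedom.
- N = 36: λ = 0.1681 × 36 × 2 / 1.5 = 8.07, power 0.788.
- N = 38: λ = 0.1681 × 38 × 2 / 1.5 = 8.52, power 0.811.

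So 38 is the smallest even N that reaches 80%. The within-between interaction at f = 0.41 would give 14 and a one-way ANOVA would give 50. Of the three, only the between-factors test gives 38.

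**2. Implied SD.** For two equal groups f = difference / (2 × SD), so SD = 15 / (2 × 0.41) = 18.3 m (18.1 to 18.5 m allowing for rounding of f). In this test it is the SD of distance at each visit. The SD of change is SD × √(2(1 − ρ)) = 18.3 × √1 = 18.3 m, the same value at ρ = 0.5.

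**3. Power at the plan's own SD and correlation, 19 per arm.**
- *Change from baseline:* noncentrality (15 / 18.29) × √(19/2) = 2.53 on 36 df, power 69%. Reaching 80% would take 25 per arm.
- *Final distance adjusted for baseline:* residual SD = 18.29 × √(1 − 0.5²) = 15.84 m, noncentrality (15 / 15.84) × √(19/2) = 2.92, power 81%. It matches the plan's figure because (1 + ρ)/2 and 1 − ρ² are both 0.75 at ρ = 0.5.
- *Time-averaged group effect, arms equal at baseline:* the averaged difference is 15/2 = 7.5 m, f = 0.205, λ = 2.13, power 30%. For f = 0.41 to hold here, the SD would have to be 7.5 / 0.82 = 9.1 m.

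**4. Other SDs.** The article gives none, so every row after the first is an assumption. Detectable difference and half-width are for change, 19 per arm.

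| SD of change | Power, change | Power, baseline-adjusted (ρ = 0.5) | Detectable at 80% (0.93 × SD) | 95% CI half-width (0.66 × SD) |
|---|---|---|---|---|
| 18.3 m (implied) | 69% | 81% | 17 m | 12 m |
| 25 m | 44% | 55% | 23 m | 16 m |
| 30 m | 32% | 41% | 28 m | 20 m |
| 40 m | 20% | 25% | 37 m | 26 m |
| 60 m | 12% | 14% | 56 m | 39 m |

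**5. Effect of a higher correlation.** With a visit SD of 30 m and ρ = 0.8, the SD of change is 30 × √0.4 = 19.0 m and power on change is 66% (70% baseline-adjusted). With a visit SD of 60 m and ρ = 0.8, the SD of change is 38 m and power is 22%.

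**The case against.** The strongest reply is that nothing printed is miscalculated. N = 38 and 80% power do follow from f = 0.41, and the SD behind f may stand in the cited source or in a fuller protocol that is not shown. This stands in part. A reader might infer that the 80% has no basis at all, which goes too far: it follows from f, and it is f that lacks a documented basis.

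A reader might also infer that 18.3 m is not credible because it is smaller than the 30 m minimal difference, or because the patients are varied. The article does not support this. A minimal important difference is a mean change and sets no floor under an SD. No walk distances or spread are reported. The exclusions (body mass index limits, lung and orthopaedic disease, smokers, regular exercisers) and the use of the better of two tests would tend to narrow the spread.

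Two further points hold. The drop from 81% to 69% at 18.3 m comes from the contrast tested, not from a larger SD. And it would be wrong to say that only an extreme correlation could help: 0.8 at a visit SD of 30 m brings power on change back to 66%.

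What the reply does not answer is that the section sets out the calculation, presents f as derived from two means, and relies on a power that its own inputs do not give for a difference in change.

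**Conclusion.** The point holds as a fault in the stated power and its documentation. It does not show that the SD is false. The article derives f = 0.41 without an SD, and the value it implies is 18.3 m. Taking that SD and the correlation of 0.5 at face value, 38 completers give 69% power for a 15 m difference in change and 30% for the time-averaged group effect with equal baselines. The stated 80% is met, at 81%, only with baseline adjustment. These figures assume 19 completers per arm, a two-sided 5% level and equal SDs at both visits. Below them lies a range that depends on an SD the article does not give: 44% to 12% on change for assumed change SDs of 25 to 60 m. A correlation above 0.5 would lower the SD of change for a given visit SD.

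**What to change.** In the Sample size section:

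1. Replace the bare effect size of 0.41 by its components: a 15 m between-arm difference and a stated, sourced SD of the change in six-minute walk distance.
2. Name the contrast to be tested (change from baseline, or final distance adjusted for baseline). For that contrast and 38 completers, restate the power at 15 m and the difference detectable at 80% power, in metres (for change, about 0.93 × SD of change).
3. If no source supports an SD near 18 m, withdraw the 80% claim. Report instead the detectable difference and the expected 95% confidence interval half-width (for change, about 0.66 × SD of change).

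The cost is a rewritten paragraph and probably a less favourable power figure. No change in enrolment is asked for, and no extra visits.
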